## Methods: data collection, management, and analysis

### Data collection methods

Table 2 shows data collection according to inclusion and follow-up visits.

### Data management

An e-CRF will be developed by using the Ennov Clinical© software. The e-CRF will be managed in agreement with INSERM CIC 1415 standardized operating procedures (SOP). Data from investigating centers will be entered by using a secure web site monitored by CRA, and queries will be edited by data managers, in agreement with an a priori-specified data-management plan. Blinded review will be performed before locking the database. The database will be locked in agreement with INSERM CIC 1415 SOPs, and data will be extracted in a SAS format or other, according to statistical requirements. Raw data will be stored in XML format.

### Statistical methods

The intention-to-treat (ITT) principle will be applied. Nevertheless, participants who withdraw their consent to study participation will be discarded in case they explicitly refuse that their collected data be used, as required by the French legislation. The number of participants with missing data for each variable of interest will be indicated. Missing data will be managed using a multiple imputation approach. Variables associated to the missingness mechanism will be identified form the study data.

#### Statistical analysis of the primary outcome

Proportion of stone-free patients at 3 months will be compared between the experimental and the control groups using a logistic regression in which stratification variables will be included. The intervention effect will then be expressed as an odds ratio. In agreement with the CONSORT guidelines, the inter-group difference and its 95% confidence interval will also be estimated. For that, a linear model using an identity link function will be estimated. Missing data will be managed using a multiple imputation approach.

#### Statistical analysis of secondary outcomes

Proportion of patients with post-operative UTI within 30 days after surgery will be compared between randomization groups using the same approach as for the analysis of the primary outcome.

Visual numerical scale of pain in the recovery room, in the service, and at discharge will be analyzed using a mixed model. Proportion of patients who received opioids will be compared between randomization groups using the same approach as the one use for the analysis of the primary outcome.

Analysis of the occurrence of furosemide-related events will be descriptive.

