### Secondary outcomes

The post-operative UTI will be assessed within 30 days after surgery on the combination of fever higher than 38.5 °C and/or chills and/or clinical symptoms (supra-pubic pain, dysuria, pollakiuria, urgency, urinary burning, back pain radiating to the genitals, hematuria) and/or positive urine culture with a significant bacteriuria threshold (depends on the germ isolated and the gender of the patient) [15].

The post-operative pain will be assessed on visual numerical (from 0 to 10) pain scale in the recovery room, in the service, and at the discharge. The use of opioids will be reported.

Furosemide adverse events will be assessed.

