**Safety evaluation**							
Adverse events (serious or not)	X	X	X	X	X	X	X

^a^An ECBU may be performed in the event of postoperative urinary tract infection symptoms

^b^Blood test includes a blood count and platelet count, creatinine levels, creatinine clearance, and a blood ionogram. Other parameters may be added at the anesthetist’s request, as is standard practice

^c^Monitoring of 5 h to 7.5 h

^d^Clinical examination, blood pressure, cardiac frequency, evaluation of pain

The patient will be recruited by the urologists on the day when the indication to perform a fURS for the destruction of kidney stones is established. Initial information will be given by the urologist during this consultation. An appointment will be made with a CRA following this consultation to discuss the study in more detail and answer any questions the patient may have, particularly regarding logistical aspects. After this interview with the CRA, the patient will see the urologist again to sign his consent if he agrees to take part in the study, prior to any investigation.

The patient will be called for his/her anesthesia consultation in the month prior to the procedure, as is done in current practice. As it is usually done, an ECBU will be done 1 week before the surgery [14]. A blood ionogram and creatinine will be necessary before inclusion in the study to verify the absence of contra-indications, particularly to furosemide. This blood test should be performed 48–72 h before the surgical procedure in order to be as close as possible to the furosemide injection, if applicable.

The CRA will contact the patient by phone 1 week before the surgery to remind him/her of the necessity to perform the biological check-up 48–72 h before the surgery to verify his/her eligibility for the furosemide injection if necessary.

A urinary pregnancy test will be performed for women of childbearing age on the morning of the procedure.

The randomization will be done at the end of the fURS, if the destruction of the kidney stone is macroscopically complete. The anesthesia team injects furosemide or not, depending on the randomization of the patient.

At post-operative visit, careful monitoring will be carried out in the recovery room by the anesthetic nurses for about 2 h after the operation.

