The half-life of furosemide is 1 h to 1.5 h after injection. Considering that the product is completely eliminated from the body after 5 half-lives, a monitoring of 5 h to 7.5 h will be required to ensure optimal monitoring of patients after their injection, which corresponds to the postoperative monitoring in routine practice (in conventional or ambulatory units).

Evaluation of pain will also be assessed by nurses during hospitalization. Pain will be assessed using a numerical pain scale ranging from 0 to 10. This will be done at three time points: in the recovery room, in the service, and at the discharge.

The patient will be followed up for 3 months (± 2 weeks), after the surgery. Patients will use a follow-up book to carry out a self-assessment in particular on the UTI. As usually, patients should consult their general practitioner in the event of sign of infection. However, only the combination of some of these symptoms will be synonymous with a UTI, requiring the expertise of a general practitioner or urologist to distinguish between a real UTI and just the postoperative symptoms caused by the procedure performed in the excretory tract, corresponding to the healing of the urinary mucosa. The ECBU should only be carried out at the request of a doctor (general practitioner or urologist).

A phone call will be performed 1 month after the procedure. We will collect the potential event: fever > 38.5 °C, chills, clinicals symptoms, call or consultation with general practitioner or urologist within 30 days of surgery, ECBU performed within 30 days of surgery, antibiotics within 30 days of surgery. All adverse events presented by the patient since the intervention will be collected.

The patient will have to perform his/her low dose abdomino-pelvic CT scan without injection at 3 months after the operation (± 2 weeks).

We scheduled another phone call by the CRA at about 2 months post-operatively to remind the patient to have his non-injected low-dose abdominal-pelvic CT scan at 3 months (± 2 weeks).

The results of the CT scan should be brought back at the 3-month follow-up consultation with his/her referring urologist. The CT scan data will be interpreted by the urologist and retrieved for an anonymous reading by 2 radiologists in a blind process.

We will also collect the occurrence of UTI in the first post-operation month or other complications, using the patient’s memory and the participant diary noting information.

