## Methods: assignment of interventions

### Allocation

#### Sequence generation and allocation concealment mechanism

We will use a computer-generated randomization schedule performed by an independent statistician not otherwise involved in patient recruitment or follow-up. Randomization will be stratified by use of double J stent (yes/no), localization of the stone (inferior calix/other), and complete dusting (yes/no). We will use permuted blocks, and block sizes will not be disclosed to the study investigators to ensure concealment.

Randomization procedure will be centralized via a web-based interactive response system (CSonline) managed by the biometrical unit of the Tours University Hospital, thus ensuring allocation concealment.

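### The 30-day UTI analysis makes no use of the urine culture scheduled before surgery, and the and/or definition can count an organism already present then as a post-operative event (minor improvement)

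*Protocol article*

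**What the plan says.** All places are in the protocol article.

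- **Objectives.** Lower early post-operative UTI with furosemide is a directional secondary objective.
- **Participant timeline (Table 2 and the text after it).** A culture is scheduled before the procedure: "As it is usually done, an ECBU will be done 1 week before the surgery". After surgery no culture is systematic. A Table 2 footnote allows one for UTI symptoms, and the text limits it to a doctor's request. The same text says that only some symptoms in combination amount to a UTI, and that a doctor must separate a real infection from symptoms of mucosal healing.
- **Secondary outcomes.** The UTI outcome is a list of fever, chills and clinical symptoms, ending "and/or positive urine culture with a significant bacteriuria threshold". It does not mention the pre-operative culture and does not require the finding to be new.
- **Statistical analysis of secondary outcomes.** UTI "will be compared between randomization groups using the same approach as for the analysis of the primary outcome". The primary analysis compares the groups "using a logistic regression in which stratification variables will be included".
- **Sequence generation and allocation concealment mechanism.** The strata are double J stent, stone location (inferior calyx or other) and complete dusting.
- **Exclusion criteria.** A positive pre-operative culture is not an exclusion. Needing an aminoglycoside or vancomycin before or during the procedure is, which may remove some culture-positive patients.

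**The concern.** A binary culture result is scheduled before randomization for everyone, and the same kind of result is part of the outcome. Using the baseline version of an outcome component as a covariate is ordinary practice and nearly free. The stated model omits it.

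Separately, the outcome as worded can include bacteriuria that predates the injection. A single injection after surgery cannot have prevented an organism from being there a week earlier. Any such patient counted on culture alone adds an event that does not bear on the objective. Events of this kind, spread equally over both arms, raise both rates and pull the contrast toward no effect.

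**Working it through.** **1. The plan's own figure.** Inputs from Sample size: 85% versus 95%, two-sided 5%, power 90%, 1:1 allocation. With pooled variance under the null:

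n per arm = [1.96·√(2·0.90·0.10) + 1.2816·√(0.85·0.15 + 0.95·0.05)]² / 0.10² = 187.05, total 374.1.

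The stated 374 reproduces, and 374/0.90 = 415.6 gives the stated 416. I therefore use 187 per arm below. No sample size or rate is stated for UTI.

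**2. Dilution if carried-over bacteriuria is counted.** Assumption: a share c of patients in each arm is counted because of bacteriuria present before surgery, regardless of treatment. The observed rate is c + (1 − c)·p, so the difference shrinks by the factor (1 − c). Power is for two proportions, 187 per arm, two-sided 5%.

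| True rates (assumed) | c = 0 | c = 2% | c = 5% | c = 10% |
|---|---|---|---|---|
| 8% vs 4% | 37% | 29% | 22% | 16% |
| 10% vs 5% | 45% | 37% | 29% | 21% |
| 15% vs 7.5% | 63% | 56% | 47% | 37% |

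For 10% versus 5%, the observed rates become 11.8% vs 6.9%, 14.5% vs 9.75% and 19.0% vs 14.5%. The difference falls only from 5.0 to 4.9, 4.75 and 4.5 points. Most of the power loss comes from the larger variance at higher rates. If there is no true difference, the observed arms remain equal.

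**3. What the covariate buys.** Logistic simulation, 1,200 trials per scenario, 187 per arm. Assumptions: control UTI 10%, treatment odds ratio 0.47, pre-operative culture positive in 10% or 20%, odds ratio of UTI for a positive culture 2, 4 or 8. The models held treatment alone, or treatment plus culture; the stratification variables were left out.

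| Culture positive | Culture OR | Power without | Power with |
|---|---|---|---|
| 10% | 2 | 45.1% | 45.0% |
| 10% | 4 | 40.7% | 42.7% |
| 10% | 8 | 41.3% | 43.2% |
| 20% | 2 | 46.0% | 45.8% |
| 20% | 4 | 44.3% | 45.0% |
| 20% | 8 | 37.8% | 41.8% |

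The gain is about 0 to 4 points. With a treatment odds ratio of 1, rejection was 3.9% to 5.2% without the covariate and 4.2% to 5.0% with it.

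**4. Chance imbalance at baseline.** The 95% range of the between-arm difference in positive cultures is ±1.96·√(2p(1 − p)/187), which is ±6.1, ±8.1 and ±9.3 points for an assumed p of 10%, 20% and 30%. If a positive culture raised UTI risk by 30 points (assumed), this would move the UTI difference by ±1.8, ±2.4 and ±2.8 points. For scale, the whole 95% sampling range of the UTI difference at an assumed 10% rate is ±1.96·√(2·0.10·0.90/187) = ±6.1 points. The imbalance is one component of such sampling error and is not added to it.

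**The case against.** The strongest case against has four parts.

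- **Carry-over may seldom be seen.** No post-operative culture is routine, so silent bacteriuria would mostly go undetected, and the timeline text calls for symptoms and a doctor's judgement. This stands as a limit on frequency: the shares in step 2 are illustrations, not estimates. It does not close the gap. The procedure itself causes symptoms, so a patient with healing symptoms and an old organism may be cultured and, under the and/or wording, counted.
- **The covariate does not cure the definition.** This stands. Misclassified events stay in the data whatever the model, so the two changes are separate.
- **Extra covariates are often left to the analysis plan, which is not shown.** This is fair, and it is why the point is small. The article does fix the covariate set by reference to the primary model, so naming one more improves a stated analysis; it does not fill an omission.
- **A symptomatic infection arising from an earlier organism may be a genuine post-operative UTI.** This stands, and the fix keeps such patients as events.

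Some stronger readings are tempting but unsupported. A reader might infer that pre-operative bacteriuria routinely counts as an event; the documents show only that it can. A reader might infer that the culture is the best predictor of UTI collected, or that the strata were chosen with fragment clearance alone in mind; the article ranks no predictors and gives no reason for the strata. A reader might take the imbalance in step 4 as bias. Randomization balances the culture in expectation, and the confidence interval already reflects chance imbalance. Finally, the article's silence on how a positive pre-operative culture is handled does not show that bacteriuria persists to surgery.

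**Conclusion.** The point holds as a minor improvement. Two facts are established on the text: the pre-operative ECBU has no role in the UTI model, and the and/or definition, read literally, admits a positive culture alone without regard to what grew before surgery, which fits poorly with the timeline text. The comparison remains valid. Type I error stays near 5% and neither arm is favoured. The cost is some dilution, of unknown frequency, and a loss of precision worth about 0 to 4 points of power in the scenarios tried. Every size given rests on assumed UTI rates, culture prevalence and strength of association, because the article states none of them.

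**What to change.** 1. **Statistical analysis of secondary outcomes:** add the pre-operative ECBU result (positive or negative) as a prespecified covariate in the UTI model, alongside the stratification variables. If the analysis plan already does this, only the second change remains.
2. **Secondary outcomes:** reconcile the UTI definition with the Participant timeline text. State whether a positive culture alone qualifies, and that a post-operative culture growing the same organism as the pre-operative ECBU is not an event on microbiology alone.

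The cost is one covariate and one or two sentences, with no extra tests or patients. The article does not say that the organism is recorded in the e-CRF for the pre-operative and doctor-requested cultures; that must be confirmed, and the fields added if absent. According to Trial status no patient had yet been included, so both changes could be made before any outcome data existed.

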#### Ancillary analysis

An evaluation of agreement between the imaging analysis of the urologist and the specialized radiologist will be done considering the primary outcome. Urologists will assess CT scan while the study is going on, while specialized radiologists will assess the CT scan at the end of the study.

We will assess agreement between the imaging analysis of the urologist in center and the centralized reading of the CT scans using the Kappa coefficient and its 95% confidence interval. We will also estimate the agreement rate and its 95% confidence interval and we will study the discordant cases.

#### Sub-group analyses

The effect of the prescription of an alpha-blocker will be looked at considering the primary outcome.

Sub-group analyses will be performed using a modeling approach, by introducing the variable associated to the sub-groups and its interaction with the group variable. A forest plot will be drawn to report the results of these subgroup analyzes.

No interim analysis is planned as part of our study.

## Methods: monitoring

### Data monitoring

A CRA will be responsible for coordination of the study: he/she will be responsible for the logistics of and monitoring the study; producing reports concerning its state of progress, verifying that the e-CRFs are updated (request for additional information, corrections, etc.), importing CT scans and making them anonymous, and transmitting severe AEs to the sponsor. The technician will follow the SOPs.

In view of the low risk presented by the single administration of 40 mg furosemide, no data safety monitoring board (DSMB) is foreseen in this trial. In the same way, no ancillary or post-trial care or compensation is planned for this trial.

### Harms

All AEs will be monitored until they are completely resolved. The investigator will immediately notify the sponsor of any serious AE. The sponsor will report all suspected unexpected serious adverse reaction (SUSARs) to the Eudravigilance (European pharmacovigilance database), French health authorities (ANSM), and the investigators within the regulatory time periods for reporting.

### Auditing

An audit may be performed at any time by sponsor-appointed people who are independent of those responsible for the study. The aim of an audit is to ensure good quality of the study, the validity of results, and that the law and regulations in force are well observed. The investigators agree to comply with the requirements of the sponsor and the relevant authority for an audit or inspection of the study. The audit can apply at all stages of the study, from development of the protocol to publication of results.

## Ethics and dissemination

### Research ethic approval

The sponsor and the investigators undertake to conduct this study in compliance with French law no. 2004–806 of August 9, 2004, and following Good Clinical Practice and the Helsinki Declaration (Ethical Principles for Medical Research involving Human Subjects, Tokyo 2004). The study will be conducted in accordance with this protocol. With the exclusion of emergency situations requiring specific therapeutic actions, the investigators will observe the protocol in all respects, particularly in obtaining consent and the notification and follow-up of serious AEs. The protocol was approved by the institutional review board of the University Hospital Centre of Tours and received authorization from ANSM.

### Protocol amendments

Important protocol modifications will be submitted as well for approval to the Institutional review board of the University Hospital of Tours and will be communicated to coinvestigators.

### Consent and assent

The patient will give their informed signed consent after they have been orally informed of the study and have received a written information form (Additional file 1). These potential participants are informed that they are free to withdraw from the study at any moment.

### Confidentiality

During this research study or when it is over, the information collected on the people taking part in it and forwarded to the sponsor by the investigators (or any other specialized staff member involved) will be made anonymous. Under no circumstances will the uncoded names or addresses of the people concerned appear in any data.

### Access to data

The sponsor is responsible for obtaining agreement from all the parties involved in the study in order to guarantee direct access, in all the sites where the study is being conducted, to source data, source documents, and reports, to control their quality, and to audit them. The investigators will make available to people with a right of access to these documents, according to the legislative and regulatory provisions in force (articles L.1121–3 and R.5121–13 of the French Public Health Act), the documents and individual data strictly necessary for monitoring, carrying out quality control and auditing the biomedical research.

### Dissemination policy

INSERM CIC 1415 Tours will analyze the data provided by the study centers. Results will be displayed in a written report that will be submitted to the sponsor. At the end of the analysis, results will be published in ClinicalTrials.gov. The international rules for writing and publication (Vancouver Agreement, February 2006) will be followed. In accordance with law no. 2002–303 of March 4, 2002, patients will be informed, at their request, about the overall results of the study [17].

### SPIRIT

This protocol has been written in accordance with the Standard Protocol Items: Recommendations for Interventional Trials (SPIRIT) guidelines. The SPIRIT checklist is in Additional file 2. The SPIRIT figure is in Table 2.

## Discussion

Lithiasis is a public health problem. It affects about 10% of the general population. This prevalence is increasing (multiplied by 3 in 40 years) [1], partly due to changes in the population’s eating habits over the years. The lithiasis patient is a patient with a chronic disease requiring annual follow-up and who may suffer from multiple recurrences, with a recurrence rate at 5 years of 50% [1, 2].

Recurrences are partly due to residual fragments left in the kidneys at the end of the operation.

As far as residual fragments are concerned, their presence leads to an early recurrence of stones because they form the bed for a new aggregation of crystals in the kidneys. Being able to reduce the rate of residual fragments in patients with the use of furosemide at the end of the intervention therefore seems essential in the management of recurrences in our patients. This will also improve our patients’ quality of life. Indeed, lithiasis disease leads to chronic pain associated with acute pain that motivates consultations to the emergency for specialized management.

This FIRE Stones project will be the first to study the impact of furosemide injection after fURS for renal stones.

fURS for stones are performed in common practice by most urologists, both independent and practicing in hospital. In fact, more than 40,000 fURS for stones are performed per year in France. It means that the number of patients will be sufficient to conduct the study. The selected centers of this study are used to recruit in clinical studies and frequently perform this procedure. Depending on the center, an average of 90 to 200 fURS for kidney stone destruction are performed per year. Moreover, this is a pragmatic study that fits perfectly into the current practice of urologists. Its realization does not compromise the organization of the services that will participate, thus allowing a better adhesion to the protocol.

